## Abstract

**Background:**

Isometric resistance training (ISO-RT) has gained renewed attention for its potential to elicit muscular adaptations and enhance athletic performance. Unlike dynamic resistance training (DYN-RT), ISO-RT involves no joint movement or eccentric loading, making it particularly suitable for individuals with joint pathologies or those undergoing rehabilitation. Despite increasing interest, the comparative effectiveness of ISO-RT versus DYN-RT across various outcomes, including strength, hypertrophy, endurance, and recovery, remains inadequately explored.

**Aims:**

This study aims to evaluate and compare the effects of multi-angle ISO-RT and traditional DYN-RT on muscle performance, body composition, and recovery-related indicators in healthy adults.

**Methods:**

In this pilot randomised controlled trial, 20 healthy adults (≥18 years) will be randomly assigned to either the ISO-RT or DYN-RT group (n ​= ​10 per group). Both groups will complete a full-body resistance training program twice weekly for six weeks. The key distinction lies in the execution of the chest press and leg press exercises—performed isometrically in the ISO-RT group and dynamically in the DYN-RT group. All outcomes will be assessed at baseline and post-intervention.

**Analysis:**

Primary outcomes include dynamic and isometric strength. Secondary outcomes encompass muscular power, dynamic and isometric endurance, body composition (via dual-energy X-ray absorptiometry), muscle oxygenation (via near-infrared spectroscopy), and subjective recovery indicators such as sleep quality and delayed onset muscle soreness. Between-group comparisons will be conducted using appropriate inferential statistical tests to determine effect estimates and feasibility metrics.

**Discussion/implications:**

This trial will offer preliminary insights into the physiological and perceptual adaptations elicited by ISO-RT versus DYN-RT. The findings will inform the design of larger-scale trials and contribute to developing tailored, evidence-based resistance training guidelines for both clinical and athletic populations.

Key points:
1.Isometric resistance training (ISO-RT) has been shown to enhance muscular adaptations. However, it is unclear whether ISO-RT leads to greater, comparable, or lesser muscular adaptations than traditional dynamic resistance training (DYN-RT).2.This study protocol aims to advance understanding of the comparative efficacy of multi-angle ISO-RT vs. DYN-RT in enhancing muscular strength, hypertrophy, and both isometric and dynamic muscular endurance. It will also assess muscle oxygenation and subjective recovery markers such as sleep quality and muscle soreness. The findings will provide preliminary insights into the physiological and perceptual responses to these training modalities, informing future research and the design of larger-scale trials.

## Introduction

1

Resistance training (RT) is widely recognised as an effective modality for improving muscle strength and hypertrophy. Resistance training can be broadly categorised into dynamic and isometric muscle actions. Dynamic muscle actions involve joint movement and can be further divided into concentric (shortening) and eccentric (lengthening) phases [1]. In contrast, isometric muscle actions involve muscle contraction without visible joint movement. Isometric RT (ISO-RT) has a long-standing history, with anecdotal reports suggesting its use by strength and conditioning practitioners to enhance athletic performance through trial and error [2].

Isometric RT first gained scientific recognition in 1953 when Hettinger and Müller demonstrated that daily 6-s applications of ISO-RT could increase isometric strength by approximately 5 ​% per week [3]. In this study, participants performed submaximal isometric contractions (∼67 ​% maximal voluntary contraction - MVC) once daily for 6 ​s, with loads adjusted weekly to maintain relative intensity. This landmark study spurred interest in ISO-RT, leading subsequent researchers to explore its potential applications for health and performance [2,4]. Compared to dynamic RT (DYN-RT), ISO-RT offers unique adaptations. Isometric training can enhance strength at specific points in the range of motion (ROM), making it useful for targeting the weak spots in the ROM (i.e., sticking points), that may limit athletic performance [2]. Additionally, ISO-RT is often the preferred training method during rehabilitation for individuals with joint pathologies due to its ability to minimise mechanical stress on the joints. Its lower energy demand and the absence of eccentric muscle contractions also allow for faster recovery, enabling more frequent training and potentially greater cumulative adaptations over time [5].

Although promising, ISO-RT has been criticised for its joint-angle specificity, with strength gains often confined to the trained positions and showing limited transfer to adjacent angles [2]. Additionally, its capacity to induce muscle hypertrophy has been questioned - likely due to the absence of eccentric contractions and limited mechanical stimulus across a full ROM [2,4]. However, the perception that ISO-RT leads to inferior hypertrophic adaptations compared to DYN-RT may largely reflect methodological shortcomings in earlier studies, particularly the use of insufficient training volume and intensity. Given that both volume and intensity are key drivers of hypertrophy, it is plausible that well-designed ISO-RT protocols (featuring adequate load and volume) can elicit muscular growth comparable to DYN-RT. Nevertheless, few studies have directly compared hypertrophic outcomes between ISO-RT and DYN-RT under matched training conditions. Much of the existing ISO-RT research relies on suboptimal protocols and within-subject or unilateral limb designs, which are susceptible to confounding factors such as cross-education effects and baseline strength asymmetries between limbs [[6], [7], [8], [9], [10]]. Interestingly, emerging evidence suggests that multi-angle ISO-RT may promote more robust and generalised adaptations than traditional single-angle approaches, potentially mitigating these limitations and enhancing external validity [7].

Beyond muscle strength and hypertrophy, ISO-RT and DYN-RT may elicit distinct physiological and perceptual responses that influence training feasibility, recovery, and long-term adherence. For example, differences in local metabolic stress and fatigue accumulation could affect post-exercise recovery [11], yet these factors remain underexplored. Muscle oxygenation, which reflects real-time oxygen delivery and utilisation, is one such understudied variable. Although near-infrared spectroscopy (NIRS) offers a non-invasive means of assessing this, direct comparisons between ISO-RT and DYN-RT using NIRS are currently limited. Equally important are markers of recovery, such as muscle soreness and sleep quality, which can affect training tolerance and compliance over time. Despite their relevance, the influence of muscle soreness and sleep quality on adaptations and adherence across RT modalities remains poorly defined. Together, these gaps underscore the need for research that moves beyond traditional outcome measures to capture a more comprehensive understanding of responses to ISO-RT and DYN-RT.

To address these gaps, the current pilot study investigates the feasibility and preliminary efficacy of a novel multi-angle ISO-RT protocol in comparison to DYN-RT. A comprehensive set of outcomes will be evaluated, including muscular strength, hypertrophy, isometric and dynamic muscle endurance, fatigue recovery, muscle oxygenation, muscle soreness, and sleep quality. The findings will offer foundational insights to guide the design of future large-scale trials and support evidence-based integration of ISO-RT into both athletic and clinical RT settings.

## Aims

2

This pilot study explores the impact of a 6-week multi-angle ISO-RT program on physiological and perceptual outcomes, including muscular strength, hypertrophy, dynamic and isometric muscular endurance, muscle oxygenation, fatigue recovery, sleep quality, and muscle soreness.

## Methods

3

### Study design

3.1

This intervention will employ a randomised controlled trial (RCT) design. Eligible participants will be randomly assigned to the groups of ISO-RT (n ​= ​10) and DYN-RT (n ​= ​10). They will perform 6 weeks of training under the supervision of researchers. The protocol consists of a 2-week baseline assessment and a 1-week familiarisation phase comprising two sessions. Following the familiarisation, the participants of both groups will undergo their respective 6-week RT interventions, during which participants will attend two sessions per week. Following the intervention period, the study will conclude with a one-week follow-up assessment. This schedule results in a total study duration of 10 weeks, during which each participant will complete 17 visits (see Fig. 1). Ethical approval for this study was granted by the University of Sydney Human Research Ethics Committee (HREC 2024/HE001016). Informed consent will be obtained from all participants before they participate in the study.

**Fig. 1 fig1:**
[figure not shown]
Intervention timeline.

### Participant allocation and intervention protocol

3.2

Eligible participants will undergo a 1-week familiarisation period before being randomly assigned to one of two 6-week full-body RT programs. Both groups will consist of two training sessions per week, following identical protocols for most exercises. Both groups will train twice weekly using an identical protocol for five out of the seven prescribed exercises: seated row, biceps curl, triceps pushdown, knee extension, and knee flexion. The training programs for both groups will be identical, except for the chest press and leg press exercises. In the ISO-RT group, the chest press and leg press will be performed isometrically. Participants will be instructed to exert maximal effort during each repetition to reflect real-world applications of ISO-RT better. Each repetition will consist of a 5-s contraction at 100 ​% effort executed at three distinct joint angles (lower third, mid-range, and upper third of the ROM). Joint angles for the chest and leg press will be determined using a goniometer during the initial familiarisation session and replicated consistently throughout the intervention and during baseline and follow-up testing sessions. In contrast, the DYN-RT group will perform the chest press and leg press exercises dynamically using a 2-1-2 repetition cadence (2-s concentric, 1-s pause, 2-s eccentric) at 80 ​% of their one-repetition maximum (1RM). In both groups, these exercises will be performed for three sets of six repetitions, with a 2-min rest between sets. The remaining five exercises will be identical across both groups, performed through the full ROM using a controlled 5-s repetition tempo. The target intensity will correspond to a perceived exertion of 7–9 out of 10 on the Borg CR10 scale, with inter-set rest intervals of 90–120 ​s. Prior to the chest press and leg press, participants in both groups will complete two standardised warm-up sets consisting of five repetitions at ∼50 ​% and ∼70 ​% of their maximal strength levels (1RM for the DYN-RT group and MVC for the ISO-RT group).

Table 1 provides details of the training intervention protocols.

**Table 1 tbl1:** Training Intervention Protocols (performed twice per week).

Exercise Order	ISO-RT Group	DYN-RT Group
**1 & 2**	Isometric CP and LP, 3 sets^a^ x 6 repetitions (5 ​s per repetition) @ effort to produce 100 ​% MVC. 120-sec rest b/w sets	Dynamic CP and LP. 3 sets x 6 repetitions (2-1-2 cadence) at 80 ​% 1RM. 120-sec rest b/w sets
**3**–**7**^b^	Exercises: SR, TP, KE, KF, BC. 3 sets x 8–10 repetitions @ RPE of 7–9/10. 90–120 ​s rest b/w sets	

Abbreviations: b/w ​= ​between; CP = Chest Press; KE = Knee Extension; KF = Knee Flexion; LP ​= ​Leg Press; sec ​= ​seconds; SR = Seated Row; TP ​= ​Triceps Pushdown; BC= Biceps Curl, 1RM ​= ​one-repetition maximum; RPE ​= ​rate of perceived exertion.

a With each set, it will perform at a different angle (lower, middle, upper range of motion - ROM).

b Participants will follow an identical exercise training protocol in both groups, except for the chest press and leg press, which will be performed isometrically in the ISO-RT group and dynamically in the DYN-RT group.

### Training equipment and isometric force monitoring setup

3.3

All resistance exercises except bicep curls, which will be performed with free weights, will be executed using Keiser A400 pneumatic resistance machines (Keiser Sports Health Equipment, Fresno, California, USA), which enable precise control of resistance and movement velocity through pneumatic load modulation (see Fig. 2). These machines are commonly used in both clinical and high-performance settings due to their smooth resistance profiles and real-time feedback capabilities. For the isometric chest press and leg press exercises, a custom-engineered actuator system has been developed to fix the machine arms at specific joint angles, effectively transforming the dynamic Keiser machines into isometric testing and training platforms. The actuator assembly, which mounts directly to the pneumatic cylinder housing, securely restricts joint movement at predefined angles using a high tolerance locking mechanism (see Fig. 3). This setup allows participants to perform isometric contractions at consistent joint positions across all sessions.

**Fig. 2 fig2:**
[figure not shown]
Keiser A400 pneumatic resistance machines: (a) Biaxial leg press and (b) Biaxial seated chest press.

**Fig. 3 fig3:**
[figure not shown]
Load cell integrated with the custom-engineered actuator system on the Keiser pneumatic resistance machine.

To quantify force output during isometric contractions, each actuator is fitted with an AMA XTRAN® strain gauge-based load cell (Australia). The transducer transmits force data via USB-C to a laptop running ISOTrainer V1.1, a custom-built software application developed specifically for this study (see Fig. 4). The ISOTrainer interface allows real-time monitoring and recording of applied force through two independent channels (Channel 0 and Channel 1). A key feature of ISOTrainer is its live visual feedback module, which displays real-time force traces on a dual–axis graph interface (see Fig. 4). Participants will receive immediate visual feedback on their contraction force and for the muscle endurance test will receive feedback relative to individualised target thresholds (e.g., 80 ​% MVC), represented by upper and lower yellow limit lines. This supports consistent effort regulation and engagement during repeated isometric trials and training sets. All force data are time-stamped and automatically saved in structured output files for subsequent analysis. This integrated hardware-software setup allows for high-fidelity, reproducible measurement of isometric force production, while enhancing participant engagement and test standardisation through visual biofeedback.

**Fig. 4 fig4:**
[figure not shown]
ISOTrainer V1.1 interface displaying real-time isometric force output with visual feedback and target thresholds from dual-channel load cell inputs.

### Eligibility criteria

3.4

Participants will be eligible for this study if they meet the following conditions: they are males or females aged 18 years or older; have not engaged in structured RT within the past three months; do not have any clinical conditions; have no musculoskeletal injuries; are able to provide written informed consent and complete study measures in English; and are willing and able to attend both pre- and post-intervention exercise testing and twice weekly training sessions across an 6-week period at the University of Sydney's Susan Wakil Health Building (Sydney, NSW, Australia).

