### Sample size

5.1

As this is a pilot study with an exploratory focus, no formal a priori power calculation has been conducted, as the primary objective is not to test hypotheses but to estimate effect sizes, assess outcome variability, and evaluate the feasibility of the intervention protocol. Moreover, due to the limited availability of previous studies employing comparable designs (i.e., directly comparing isometric and dynamic RT on strength and body composition), there is insufficient data to support a reliable power analysis at this stage. Based on methodological recommendations for pilot trials, a total sample size of 20 participants (10 per group) is considered appropriate for this phase of investigation. This is consistent with established guidance suggesting that 10–12 participants per group are sufficient to estimate key design parameters such as effect size variability, adherence, and procedural feasibility in small-scale studies [16,17]. Although the sample is not powered to detect statistically significant between-group differences, post hoc sensitivity analysis indicates that, with an alpha of 0.05 and 80 ​% power, the study would be able to detect very large effect sizes (Cohen's d ​≥ ​1.2). While detecting effects of this magnitude would suggest strong intervention potential, the primary aim of this study is to generate preliminary data to inform the design and powering of an adequately powered trial in the future.

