### Data analysis plan

5.2

The effects of ISO-RT vs. DYN-RT on primary outcomes (isometric and dynamic muscular strength and power) and secondary outcomes (muscle hypertrophy, muscular endurance, and muscle oxygenation) will be analysed using a two-way repeated measures ANOVA, with time (pre- and post-intervention) as the within-subject factor and group (ISO-RT vs. DYN-RT) as the between-subject factor. Where significant main effects or interactions are observed, Bonferroni-adjusted post hoc tests will be used to determine pairwise differences. To compare between-group percentage changes in outcome variables (e.g., strength, power, isometric and dynamic muscular endurance, hypertrophy) a one-way ANOVA will be conducted, followed by Bonferroni correction for multiple comparisons. All analyses will be conducted using SPSS software (Version 29.0; IBM Corp., Armonk, NY, USA), with statistical significance set at p ​< ​0.05.

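### With arms of 10 open to both sexes, no stratification described and no sex term in the model, chance sex imbalance adds avoidable noise to the pilot's effect estimates if training gains differ by sex

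*Protocol article*

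**What the plan says.** **Who enters.** Eligibility criteria (3.4) admits both sexes with no upper age limit: "they are males or females aged 18 years or older".

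**How they are allocated.** Study design (3.1) says: "Eligible participants will be randomly assigned to the groups of ISO-RT", with 10 in each arm. Participant allocation and intervention protocol (3.2) adds the timing: "Eligible participants will undergo a 1-week familiarisation period before being randomly assigned to one of two 6-week full-body RT programs". Sex is therefore known before allocation. The article names no stratum, block or minimisation factor. Nor does it say that allocation is unstratified.

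**How they are compared.** Data analysis plan (5.2) fixes a repeated-measures ANOVA "with time (pre- and post-intervention) as the within-subject factor and group (ISO-RT vs. DYN-RT) as the between-subject factor". No other factor or covariate is named. A second analysis is a one-way ANOVA: "To compare between-group percentage changes in outcome variables".

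**What the trial is for.** Sample size (5.1) states that "a total sample size of 20 participants (10 per group) is considered appropriate" and that the aim is to estimate effects, variability and feasibility, not to test hypotheses.

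**The concern.** Strength (1RM and MVC), power and DEXA lean mass are measured in absolute units, and absolute gains may well be larger in people who start stronger. If so, men and women will differ in their pre-post change. With only 10 per arm, randomisation can leave the arms unequal in sex. A model with group and time alone then assigns part of the sex difference in change to the training method.

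The product at risk is the one the pilot exists to deliver: the effect estimate that will inform the design of a larger trial. Leaving sex out of the model also leaves any between-sex variation in the residual SD.

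**Working it through.** **1. The plan's own figure.** Section 5.1 reports that "the study would be able to detect very large effect sizes", namely d of 1.2 or more with alpha 0.05, 80% power and 10 per arm. The detectable d is 1.16 by a one-sided t-test, 1.25 by the two-sided normal formula, (1.96 + 0.84) × √(2/10), and 1.32 by a two-sided t-test. Power at d = 1.2 by two-sided t is 72%. The stated figure is slightly optimistic for a two-sided test. That is a separate matter; d = 1.2 serves here only as a benchmark.

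**2. Inputs.** From the article: 20 participants, 10 per arm, both sexes, and a group × time model, which for two time points is a comparison of pre-post changes. Assumed, because the article gives no figure: 10 men and 10 women as the central case (4 to 14 men as the range), and a sex difference in the change, δ, of 0 to 2 within-sex SD.

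**3. Chance of imbalance without strata.** The number of men in one arm is hypergeometric. There are C(20,10) = 184,756 equally likely allocations.

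- 7:3 or worse: 2 × (14,400 + 2,025 + 100 + 1)/184,756 = 17.9%.
- 6:4 or worse: 65.6%.
- 8:2 or worse: 2.3%.
- 8 men and 12 women, 6 v 2 men or worse: 2 × (28×495 + 8×220 + 66)/184,756 = 17.0%.
- For even numbers of men from 4 to 14, a difference of four or more men between arms: 9% to 18%.

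**4. Shift in the estimate.** Shift = (difference in proportion of men) × δ.

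| Split | δ = 0.3 SD | δ = 1 SD | δ = 2 SD |
|---|---|---|---|
| 6:4 v 4:6 | 0.06 | 0.2 | 0.4 |
| 7:3 v 3:7 | 0.12 | 0.4 | 0.8 |

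**5. Precision over all allocations.** The variance of the number of men in an arm is 10 × 0.5 × 0.5 × 10/19 = 1.316 (SD 1.147). The difference in proportions therefore has SD 2 × 1.147/10 = 0.229. The SD of the estimate without strata or sex term is √(0.2 + 0.229²δ²), which is 0.45, 0.46, 0.50 and 0.64 at δ = 0, 0.5, 1 and 2. With 5:5 in each arm it is √0.2 = 0.45 throughout. At δ = 1 the variance ratio is (0.2 + 0.0526)/0.2 = 1.26, so chance sex imbalance costs about as much as losing a fifth of the sample (1 − 1/1.26 = 0.21).

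**6. Power at d = 1.2 and type I error** (simulated change-score comparison, 10,000 runs per cell, 10 men and 10 women; Monte Carlo error √(0.7×0.3/10,000), about half a percentage point).

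| Design and model | Power, δ = 0 | δ = 1 | δ = 2 | Type I error, δ = 1 | δ = 2 |
|---|---|---|---|---|---|
| No strata, no sex term | 72% | 61% | 41% | 5% | 5% |
| No strata, sex term | 69% | 69% | 70% | 5% | 5% |
| Strata, no sex term | 72% | 62% | 38% | 2.8% | 0.5% |
| Strata and sex term | 71% | 71% | 71% | 5% | 5% |

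**7. Why strata alone make the test conservative.** With 5:5 in each arm the estimate's true standard error is 0.45. The residual, however, still contains the sex variation: its mean square is about 1 + 5δ²/18. At δ = 1 that is 1.28, and the standard error the test uses is √(1.28 × 0.2) = 0.51.

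**The case against.** The best case on the other side has five parts.

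**The article is silent, not explicit.** A reader might infer that allocation is unstratified. The text does not support that: it gives no sequence details at all, and a condensed article may leave them to the full protocol. This stands, so the allocation half of the point is conditional. The analysis half is not, because section 5.2 states the factors of the model.

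**A marked imbalance is not likely.** This also stands. A 7:3 split or worse has probability 18% at most across the even mixes tested. Only a mild one, 6:4 or worse, is more likely than not.

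**Sex differences in level cancel.** A reader might infer that, because men are stronger, any excess of men biases the result. In the group × time contrast it does not; only a sex difference in the change matters. Gains proportional to baseline also cancel in the percentage-change ANOVA, which is affected only if percentage gains differ by sex. The group main effect would carry level differences, but it is not the contrast that measures the training effect.

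**The harm is modest unless sex matters a great deal.** At δ = 0.5 the SD of the estimate is 0.46 against 0.45, and type I error stays near 5% without strata. Nor does imbalance itself distort the within-arm SD much: √(1 + 0.21) = 1.10 at 7:3 against √(1 + 0.25) = 1.12 at 5:5, with δ = 1. All true. The harm is lost precision and a shift in the realised sample, not an invalid test.

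**The sex term does most of the work.** Also true: 69–70% power with the term alone and 71% with both. Stratification by itself is therefore no remedy, and it is not free. That governs how the fix is built; it does not remove the reason for one.

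**Conclusion.** The point holds as a worthwhile improvement, not as an error that invalidates the trial. Both sexes enter arms of 10, no stratification is described, and the stated model omits sex. If the absolute change differs by sex, chance imbalance adds noise to the estimates the pilot is meant to supply.

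The size depends on δ, for which the documents give nothing. At δ = 0 there is no harm. At δ = 1 SD, a 7:3 split shifts the estimate by 0.4 SD, and power at d = 1.2 is 61% under the stated model against 71% with strata and a sex term. At δ = 2 SD, it is 41% against 71%. These figures assume 10 men and 10 women, normal changes with equal variance and the same training effect in both sexes. Age, also left open by the eligibility criteria, is not quantified here.

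**What to change.** 1. **Data analysis plan (5.2):** add sex as a between-subject term to the group comparisons, in both the repeated-measures ANOVA and the percentage-change ANOVA. In the repeated-measures model, sex must enter with its interaction with time, since that is what adjusts the group × time contrast. A group × sex term is not needed.
2. **Study design (3.1) and Participant allocation (3.2):** state whether allocation is stratified by sex. Unless the full protocol already does so, allocate 1:1 within sex using permuted blocks. Allocation follows familiarisation, so sex is available in time.

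Make both changes together. Strata without the sex term bring type I error to about 3% at a 1 SD sex effect and gain no useful power.

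**Cost.** One residual degree of freedom: if sex has no effect, power at d = 1.2 (noncentrality 1.2 × √5 = 2.68) goes from 71.8% on 18 degrees of freedom to 71.5% on 17. Two allocation lists replace one. If the sexes have odd counts, such as 9 men and 11 women, both lists can end one over in the same arm and give 11:9 overall; unfinished blocks larger than two can add to this. No extra participants, visits or procedures are needed.
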